# A Technology-Enhanced Medical Nutrition Therapy and Diabetes Self-Management Education for Adults With Disability and Type 2 Diabetes: Protocol for a Pilot and Feasibility Randomized Controlled Trial

**DOI:** 10.2196/71495

**Published:** 2025-09-26

**Keywords:** diabetes mellitus, telehealth, persons with disabilities, diabetes self-management education, medical nutrition therapy

## Abstract

**Background:**

Diabetes mellitus (DM) is a serious chronic disorder that affects many individuals globally, particularly persons with disabilities, and has long-term adverse effects on the health of individuals and society. Effective self-management education is therefore required. Diabetes management focused on medical nutrition therapy (MNT) and diabetes self-management education (DSME) combined with telehealth technology has the potential to increase the active performance of diabetes management behaviors among persons with disabilities and improve their overall quality of life and quality of self-care.

**Objective:**

This study aims to evaluate the impact of different levels of technology on the delivery of MNT and DSME among persons with disabilities.

**Methods:**

The study is a single-blinded, 3-arm, randomized controlled trial among adults living with both type 2 diabetes and a permanent physical disability. Web-based recruitment is done through partner organizations. The target sample size is 90 participants randomized into 3 arms: a high-technology, a low-technology, and an attention control arm. The high-technology arm receives diabetes-related materials weekly through mediums such as email, a telehealth platform, and text; the low-technology arm receives only 1 weekly email with diabetes-related material; and the attention control arm has no technology support. The intervention is provided by a certified diabetes care and education specialist. Using multivariate linear mixed models, the study examines the relationships between the level of technology intervention and DM self-management behaviors, self-efficacy, and reductions in glycated hemoglobin (HbA_1c_). The primary outcome is the proportion of participants in each group with improved self-management behaviors, as measured by several validated questionnaires. The secondary outcome is a better HbA_1c_ reduction. Outcomes are measured at baseline and at 6 months. Questionnaires and HbA_1c_ measures will be used to measure outcomes.

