**Primary outcome measures**			
	Diabetes quality of life	Diabetes Quality of Life Measure	Baseline, postintervention
	Psychological distress	Diabetes Distress Scale	Baseline, postintervention
	Self-efficacy	Diabetes Empowerment Scale	Baseline, postintervention

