**Other prespecified outcome measures**			
	Physical activity	Godin Leisure-Time Exercise Questionnaire	Baseline, postintervention
	Dietary intake	The UK Diabetes and Diet Questionnaire	Baseline, postintervention
	Medication adherence	Medication Adherence Rating Scale	Baseline, postintervention
	Health dashboard usability	System Usability Scale	Baseline, postintervention

^a^HbA_1c_: glycated hemoglobin.

After participants receive the initial survey packet, a member of the research team calls the participants within a week. The purpose of this call is to welcome participants into the study and go over study components. During the call, the research personnel informed participants that they will receive a laboratory requisition in their mail within a week, allowing them to visit a third-party clinical testing company location to have their blood glucose tested at no cost. The research staff also lets participants know that they will be randomized into 1 of the 3 intervention groups. Participants were not informed about which intervention was the primary focus or “intervention of interest” versus the comparator groups.

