### Sample Size

In total, 90 participants will be enrolled, divided into 3 groups of 30 participants each (low-technology, high-technology, and attention control). The sample size is determined based on the primary use of analysis of covariance and uses a 2-sided test with a type I error rate of 0.05. An intention-to-treat analysis and multiple imputations are incorporated. Given a minimum correlation of 0.7 between the baseline and follow-up outcomes, there will be an 80% chance of detecting an effect size of 0.65.

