#### Primary Outcome Measures

##### Quality of Life

Participants will fill out the Diabetes Quality of Life Measure, a 15-item questionnaire that explores perceptions regarding one’s capacity to manage diabetes alongside other aspects of life [39].

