##### Psychological Distress

The Diabetes Distress Scale, a 17-item questionnaire evaluating emotional distress associated with diabetes, will be used to measure participants’ psychological distress. This scale has demonstrated validity and reliability in measuring diabetes-related emotional distress [40,41].

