##### Self-Efficacy

Participants’ psychosocial self-efficacy in diabetes management is assessed using the Diabetes Empowerment Scale Short Form. This 8-item questionnaire explores attitudes concerning diabetes and the capability to effectively manage the condition. The Diabetes Empowerment Scale Short Form has exhibited validity and reliability as a measure of psychosocial self-efficacy [42].

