### Analyses

#### Statistical Analysis

Descriptive statistics will be prepared to show the sample statistics and analyzed separately for baseline and 6-month postproject. Paired 2-tailed *t* tests and chi-square tests will be used to assess the change in continuous and discrete outcomes from baseline to 6 months for each arm. Furthermore, within-group differences will be assessed using 2-tailed *t* tests (paired and unpaired) and chi-square tests.

Multivariate linear mixed models will be used to assess repeated measures with continuous outcomes, assess the joint effects of baseline measures on 6-month outcomes, and account for the correlation between repeated measures. Quality control analyses will be performed, including assumption checking, estimating descriptive statistics of participant attrition and overall instrument completion, and investigating missingness patterns. Key variables at baseline will be examined to evaluate whether there is any systematic variation between the study groups. A participant who no longer participates in study activities will be considered lost to follow-up. App analytics on key performance indicators will be used for participants who are lost to follow-up. We anticipate the loss to follow-up rate to be approximately 20%. The primary analysis will follow the intention-to-treat principle, including all participants as originally assigned regardless of adherence. Secondary or compliance analyses will be considered if appropriate.

All qualitative data collected in the study will be content analyzed using NVivo (Lumivero), a qualitative data analysis software [48], including qualitative data collected for the feasibility, acceptability, and fidelity of interviews and meeting notes. The steps for content analysis include (1) transcribing audio recordings, (2) checking transcription against recordings for accuracy, (3) developing coding categories, (4) assigning codes to text, and (5) reviewing coded data to identify themes across the dataset.

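### The article declares two incompatible primary outcomes: a proportion with improved self-management behaviours, and three psychosocial scales; the sample size and main model fit only scores

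*Protocol article*

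**What the plan says.** The article gives two accounts of what is primary.

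- **Abstract, Methods:** "The primary outcome is the proportion of participants in each group with improved self-management behaviors, as measured by several validated questionnaires". This is a binary variable per participant, and the construct is behaviour. The preceding sentence of the Abstract has linear mixed models examine behaviours, self-efficacy and HbA1c reduction, as three separate targets.
- **Recruitment, Table 1 and Outcomes:** Recruitment refers the reader to Table 1 for the primary measures. Table 1 lists three instruments, starting with the "Diabetes Quality of Life Measure". Outcomes describes them as "a 15-item questionnaire that explores perceptions regarding one’s capacity to manage diabetes alongside other aspects of life"; "a 17-item questionnaire evaluating emotional distress associated with diabetes, will be used to measure participants’ psychological distress"; and, for self-efficacy, "This 8-item questionnaire explores attitudes concerning diabetes and the capability to effectively manage the condition".
- **Behaviour questionnaires:** physical activity, dietary intake and medication adherence appear in Table 1 under "Other prespecified outcome measures", below HbA1c, the secondary outcome.
- **Sample Size:** "The sample size is determined based on the primary use of analysis of covariance", with 30 per arm, two-sided alpha 0.05, correlation 0.7, effect size 0.65 and 80% power.
- **Statistical Analysis:** "Multivariate linear mixed models will be used to assess repeated measures with continuous outcomes". Chi-square tests are named for change in discrete outcomes within each arm, and again for within-group differences. Expected loss to follow-up is about 20%.
- **Hypotheses:** the end of the Introduction hypothesises about behaviours and HbA1c. Results hypothesises about behaviours and self-efficacy, named separately, and about HbA1c.

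**The concern.** The two accounts differ in construct and in variable type. Following the Abstract, the trial succeeds or fails on how many participants improve in what they do. Following Table 1, it succeeds or fails on scores for perceived quality of life, distress and empowerment. These can give different answers from the same data, and the article gives no rule for which one counts. An unseen SAP could supply a cut-off for improvement or a scoring rule, but it cannot make both published declarations true.

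The sizing and the main model also belong to only one of the two accounts. A baseline-to-follow-up correlation, a standardised effect and a linear mixed model all presuppose a score. If the proportion is the primary outcome, the 80% power statement does not describe it, and no comparison of that proportion between arms is set out.

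**Working it through.** **1. Construct, side by side.** The Introduction describes self-management as actions: planning meals, exercising, monitoring glucose, taking medication. The three primary scales are described in terms of perceptions, emotional distress and attitudes. Two of them touch on capacity or capability to manage diabetes, so the link to self-management exists but is indirect. Self-efficacy cannot simply stand in for behaviour, because the Abstract and the Results hypotheses list the two separately. The questionnaires closest to the Introduction's actions are in the lowest outcome tier.

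**2. Variable type, side by side.** Abstract: proportion. Sample Size: ANCOVA. Statistical Analysis: linear mixed model for continuous outcomes, and chi-square within arms. No between-arm analysis of a proportion is stated.

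**3. The plan's 80%.** Inputs from Sample Size: 30 per arm, alpha 0.05 two-sided, r = 0.7, effect 0.65 SD. From Statistical Analysis: 20% loss, so 30 × 0.8 = 24 completers per arm.

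ANCOVA residual SD = √(1 − 0.7²) = √0.51 = 0.714.

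- Pairwise at 0.05, 30 per arm: 0.65 / (0.714 × √(2/30)) = 3.53; power = Φ(3.53 − 1.96) = 94% (93% with the t distribution).
- Pairwise at 0.05, 24 per arm: 0.65 / (0.714 × √(2/24)) = 3.15; power = Φ(3.15 − 1.96) = 88% (87% with t).
- Pairwise at 0.05/2, 24 per arm: Φ(3.15 − 2.24) = 82% (about 80% with t).
- Three-arm F-test, means 0, 0.325 and 0.65, 24 per arm: noncentrality = 24 × (0.325² + 0.325²) / 0.51 = 9.94; power 79.4%.

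So 80% is reproducible as a continuous-outcome figure under either of the last two set-ups. The article does not say which was used, or which contrast the 0.65 refers to.

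**4. The same effect on a proportion.** Assumptions, none of them in the article: the 0.65 SD shift applies to one pairwise contrast; change scores are normal; improved means crossing a fixed cut on the change score; the proportion of controls who improve is 30% to 60%.

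SD of change = √(2 × (1 − 0.7)) = √0.6 = 0.775, so the shift is 0.65 / 0.775 = 0.839 SD of change. The proportion improved in the better arm is Φ(Φ⁻¹(control proportion) + 0.839). Power is for a two-arm Pearson chi-square at 0.05, summed over the exact binomial distributions.

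| Controls improved | Better arm | Power, 30 per arm | Power, 24 per arm |
|---|---|---|---|
| 30% | 62% | 73% | 66% |
| 40% | 72% | 73% | 65% |
| 50% | 80% | 69% | 61% |
| 60% | 86% | 65% | 56% |

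The normal approximation gives slightly lower values: 64% to 72% and 54% to 62%. By that approximation, 80% power needs 37 to 44 completers per arm. Dividing by 0.8 for losses gives 47 to 55 randomised per arm, or 141 to 165 in total, against 90 planned.

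**5. If all three scales stay primary.** Testing each at 0.05 gives a chance of at least one false positive of 1 − 0.95³ = 14.3% under independence.

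**The case against.** The strongest defence is that the weight of the text favours one reading. Recruitment, Table 1 and Outcomes agree on the three scales. Sample Size and the main model agree on continuous methods. The Abstract itself pairs its outcome with linear mixed models, and the word proportion occurs in one sentence only. It may be loose wording, with no responder analysis intended. That is fair for variable type, and it is why the power figures are conditional. It does not remove the construct conflict, because the hypotheses in the Introduction and in Results are also about behaviours.

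Four stronger readings are tempting, and the document does not support them.

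- **That no stated method suits a proportion.** Chi-square tests for discrete outcomes are named. The gap is that they are placed within arms. The mention of unpaired t tests in the same sentence may hint that a between-arm comparison was meant, but the text says within-group.
- **That the primary scales do not measure self-management at all.** Two of the descriptions mention capacity or capability to manage diabetes. Indirect is the fair word.
- **That dichotomising costs a fixed number of power points measured from about 93% or 94%.** That comparator is a pairwise ANCOVA at 0.05 with 30 per arm, which Sample Size does not specify; its stated figure is 80%. Nor is a 50% improvement rate in controls a safe single value, since the control arm receives the full class programme.
- **That the sponsor is free to choose the outcome after seeing the data.** The trial is registered and a full protocol is available on request. Neither is shown here, so this cannot be established.

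**Conclusion.** The point stands as an internal contradiction. The article declares a behaviour proportion in one place and three psychosocial scales in another, and sizes and models the trial only for scores. This rests on the text alone and needs no calculation.

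The numerical consequence is conditional. If the proportion is primary, the stated 80% does not carry over: power is about 65% to 73% with 30 per arm and 56% to 66% with 24 per arm, under the assumptions in step 4 of the working. If the three scales are primary, the power statement has the right variable type, but the question answered is no longer the one in the Abstract and hypotheses. It should be settled before the analysis, because it determines what the trial's main result is.

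**What to change.** Before unblinding, state the same primary outcome (construct, instrument and variable type) in the Abstract, Table 1, the hypotheses and Statistical Analysis, and give a between-arm analysis and a sample-size basis that match it. Several choices would resolve the conflict:

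- **One score.** The simplest option that fits Sample Size is the 6-month score on one named instrument that is already collected, analysed by ANCOVA with its baseline score, with the proportion improved reported descriptively. If the question is behaviour, that instrument should be one of the behaviour questionnaires. If it is self-efficacy or another psychosocial construct, the primary outcome and the hypotheses should say so.
- **Several primary scales.** Keep them, and control multiplicity across them.
- **The proportion.** Keep it, define the between-arm test, and restate the power.

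The cost is wording, since every instrument is already in the survey packet, and Data Management says that the principal investigator and primary statistician remain blinded to allocation. The downside is that measures not chosen become secondary or, under the second and third options, the stated power becomes less favourable.

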**Results:**

Data collection began in June 2024 with a total of 90 recruited participants. The intervention was delivered. Make-up classes were delivered to participants in any of the 3 cohorts between November 2024 and December 2024. The final 3-month follow-up classes were held for each cohort 3 months after the first class. Data analysis is anticipated to be completed in fall 2025.

**Conclusions:**

Effective self-management in DM is important to reduce complications. Using technology to deliver MNT and DSME could serve as an effective and convenient strategy for providing these interventions. However, intervention studies are required to determine the most effective level of technology for delivering MNT and DSME intervention to this target group. The YumABLE study is expected to provide new, meaningful, and detailed information about the effectiveness of technology and telehealth platforms for effectively delivering an MNT and DSME program for people living with a permanent physical disability and type 2 diabetes. The results will further improve web- and technology-based diabetes self-management interventions for people with disabilities.

**Trial Registration:**

ClinicalTrials.gov NCT06049225; https://clinicaltrials.gov/study/NCT06049225

**International Registered Report Identifier (IRRID):**

DERR1-10.2196/71495

## Introduction

Diabetes mellitus is a serious chronic disorder that has a significant adverse effect on the overall health of families, individuals, and societies worldwide [1]. According to the International Diabetes Federation, the global prevalence of diabetes among adults aged 20-79 years was approximately 537 million in 2021 [2], representing 10.5% of the global adult population [2,3]. This number is projected to rise to 783.2 million (12.2%) in 2045 [3].

In the United States, DM is one of the most prevalent metabolic conditions, which impacts about 38.4 million of the overall US population (as of 2021), representing 11.6% of the total population. Of this number, 8.7 million are unaware and undiagnosed [4]. Moreover, 97.6 million US adults aged 18 years and older have prediabetes, which usually leads to diabetes [4]. In 2022, the total estimated costs, both direct and indirect, associated with diagnosed diabetes in the United States amounted to US $413 billion [4]. Type 2 diabetes (T2D) can lead to cardiovascular disease, blindness, peripheral neuropathy, and reduced quality of life [5] and is linked with significant morbidity rates [6]. DM is a health concern among all populations; however, persons with disabilities are more likely to be affected by diabetes compared to those without such disabilities [7-10].

Diabetes management primarily relies on individuals and their families, making self-management fundamental in diabetes care [11]. T2D management involves a range of actions and choices such as meal planning, scheduled physical activity, monitoring blood glucose levels, taking diabetes medications, and effectively managing episodes of illness and low and high blood sugar levels [11,12]. These behaviors are meant to regulate blood sugar levels, reduce the risk of complications, and improve the overall health of individuals with diabetes [13].

When individuals with diabetes actively participate in their own care, they can significantly impact both the progression and development of their disease [12]. However, a significant barrier to achieving proper glycemic control appears to be the patient’s inability to maintain adequate self-care, such as poor adherence to prescribed medications and lifestyle adjustments [14]. Thus, educating individuals to self-manage their diabetes yields better health results [15,16].

The literature highlights the potential for diabetes to cause disability; however, the reverse is also possible [17]. Living with disability is associated with an increased risk of DM. A study found that mild and incident disability was associated with 28% and 40% increased diabetes risk, respectively [18]. Diabetes is a significant health concern across all populations; however, persons with disabilities are more likely to be affected. The Centers for Disease Control and Prevention points out that in 2020, approximately 16.2% of persons with disabilities in the United States had received a diagnosis of diabetes, in contrast to 7.5% of those without disabilities [9]. Persons with disabilities are at a greater likelihood of experiencing the major risk factors associated with diabetes [19] due to challenges in maintaining a healthy diet and lifestyle as well as accessing preventive care [20,21].

Physical disability broadly includes conditions affecting mobility like spina bifida and muscular dystrophy [22]. People who are blind, deaf, missing limbs, partially or completely paralyzed, or have other permanent or chronic physical limitations are considered to have a physical disability [23]. Accessibility and safety are the primary concerns with physical disability, with common issues including accessing public areas like city streets, sidewalks, ramps, and public buildings [23]. Some of these disabilities require mobility devices like prostheses, orthoses, canes, wheelchairs, crutches, or walkers [23].

While effective diabetes management is significant in enhancing overall health, persons with disabilities often face barriers that hinder their diabetes self-management [24] and usually exhibit poorer self-management behaviors [24-29]. For instance, self-management behavior was found to be poor among individuals with diabetes and physical limitations [28]; they are less likely to engage in moderate to vigorous physical activity or adhere to their medication compared to those without physical limitations [28]. Individuals with mobility difficulties may encounter challenges attending health care provider appointments related to their diabetes [28]. A study discovered that about 11% of adults with mobility disability had not visited a health professional for their diabetes within the past year [25]. Persons living with physical disabilities in general encounter several difficulties in maintaining a healthy diet [27]. A study found that factors including knowledge, fatigue, health condition, and function impairments influenced the dietary behavior of wheelchair users [27]. Similarly, Hall et al [30] discovered that the expense of healthy foods, a lack of motivation, shopping challenges, and time constraints for shopping or food preparation are significant barriers to maintaining a healthy diet among women with physical disabilities. Nonetheless, the authors noted that about 90% of participants were interested in improving their dietary habits [30]. Another study examining the nutritional status of individuals with spinal cord injury revealed significant deficiencies in essential nutrients, notably fiber, calcium, fruits, and dairy products [31].

Moreover, the participation of persons with disabilities in self-management interventions is limited [24], and their specific self-management needs and capabilities are unrecognized by health care professionals [24,25,29]. It was discovered that 47% of adults with disabilities have not received education on managing diabetes [25]. Age, gender, lack of accessibility, and low socioeconomic status have been found to impact diabetes self-care behaviors among persons with disabilities [24]. In addition, for individuals who are visually impaired, factors such as poor health, concerns about disease advancement, feelings of grief, and experiences of loss inhibit their engagement in diabetes self-care behaviors [29]. Taken together, these barriers can make self-management more challenging particularly for individuals with a physical disability and T2D.

A systematic review of factors influencing the adoption of diabetes management technologies identified monthly income, gender, age, educational level, and diabetes-related characteristics as key determinants of their use; however, of all 28 studies included in the review, disability status was not considered as a factor that could influence technology use in diabetes management [32]. There is limited technology-based diabetes self-management tailored specifically for persons with disabilities [33].

Recently, digital health technologies have progressively been integrated into diabetes education, functioning as either an adjunct to or a substitute for traditional in-person methods [34]. Using technology in diabetes education reduces care inequities, increases the efficacy of educational initiatives, and improves accessibility. Technology as a means of diabetes education is supported by the broad use of telehealth and digital platforms by both patients and health care professionals [35]. Patients and health care professionals have accepted the use of telemedicine and other digital tools to educate people about diabetes. The COVID-19 pandemic has, in fact, significantly increased interest in and demand for telehealth-based diabetes education. The emergence and progress of digital health technologies have resulted in several modalities for engaging and educating patients through telephone or smartphone, video or audio, web, SMS text messaging, and mobile apps, as well as combinations of these methods [35].

In this study, participants are randomized into 3 intervention groups: an attention control group, a low-technology group, and a high-technology group. The purpose of this design is to evaluate the effectiveness of varying levels of technological integration in delivering medical nutrition therapy (MNT) and diabetes self-management education (DSME). All groups receive the same frequency and quality of remote education sessions. Both the low-technology and high-technology groups receive bidirectional SMS text messaging to facilitate timely communication with a health coach. In contrast, the attention control group does not receive any text-based communication or access to a health coach. Additionally, the high-technology group receives weekly diabetes-related educational materials via multiple channels (email and text), regular text reminders (eg, to read content, track health data, and stay motivated), and access to a telehealth platform. The low-technology group receives only 1 weekly email with diabetes-related educational materials. The attention control group does not receive any supplementary educational content or access to technology-based support resources.

The aim of this study is to implement and evaluate the impact of different levels of technology on the delivery of MNT and DSME among persons with mobility disability and T2D. We hypothesize that participants in the high-technology group will have improved self-management behaviors and better glycated hemoglobin (HbA_1c_) reduction compared to their counterparts in the low-technology and the attention control groups.

